### Participant timeline {13}

#### Sample size {14}

Sample size calculation was performed through the GPower software (version 3.1). The calculation was based on the study by Schmitt et al. [20], using the main outcome (SPADI questionnaire) to detect a mean difference of 16.8 points, considering a power of 80% and an Alfa of 5%. The sample size suggested was 16 per group; however, to account for possible withdrawals that may occur in this type of study, it will be increased by 20%, thus totaling 40 participants (20 per group).

#### Recruitment {15}

Participants will be recruited from the local community through posters, leaflets distributed on university premises, health service centers in the city of Talca, and physiotherapy clinics in the region. Recruitment will also occur through social media and personal invitation.

## Assignment of interventions: allocation

### Sequence generation {16a}

A researcher will generate the sequence number through a randomization on the GraphPad software. Participants will be randomly assigned, in a 1:1 ratio, to one of the two groups studied (1) SRG or (2) SAG.

### Concealment mechanism {16b}

After the sequence is generated, sealed envelopes containing the numbers “1” or “2” will be prepared according to the predefined sequence.

### Implementation {16c}

The allocation sequence will be generated by a researcher blinded to the study protocol. Sealed and opaque envelopes in numerical order will be ready to be used after the baseline assessments, when the envelop will be unsealed by the researcher MFQ. Figure 2 presents a flowchart illustrating the experimental design of the present study.

**Fig. 2 Fig2:**
[figure not shown]
Flowchart illustrating the experimental design of the present study

## Assignment of interventions: blinding

### Who will be blinded {17a}

This will be a single-blinded study. The researchers responsible for outcome assessments, data entry, and statistical analysis will be blinded to the group assignments; they will not have access to the patient’s rehabilitation place, nor to any information related to the intervention.

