## Data collection and management

### Plans for assessment and collection of outcomes {18a}

For shoulder pain all measurements will be performed on the symptomatic side. In the case of bilateral pain, the side with greater severity will be considered in the study as proposed in previous studies [16]. However, treatment will be carried out bilaterally. To minimize bias, the evaluator responsible to measure the outcomes will be blinded to the type of treatment performed. The assessments and treatment protocols will be carried out in the Clinical Research Laboratory in Kinesiology at the university. Data such as blood pressure, heart rate, saturation, and rating of perceived exertion will be measured before, after, and throughout the rehabilitation sessions. If the patient presents signs or symptoms of hypoglycemia; glycemia > 200 mg/dl or <80 mg/dl; systolic blood pressure > 180 mmHg, or diastolic blood pressure > 100 mmHg at rest, the session or evaluation will be immediately suspended, and the necessary measures will be taken. The same evaluator will perform all the tests and evaluative measures of the variables described below.

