#### Supraspinatus tendon thickness measurement

Ultrasonographic measurement for each participant’s supraspinatus tendon thickness will be scanned by using a Lumify Ultrasound in conjunction with a 4–12-MHz linear transducer (Philips Medical System) on musculoskeletal program. The protocol of the ultrasound measurement will be designed by an experienced sonographer in musculoskeletal ultrasound scanning. All ultrasound scanning will be performed by the researcher responsible of the study. Ultrasound images will be captured with the patients seated in an upright position, feet flat on the floor, neutral trunk posture, and head facing forward, evaluating supraspinatus tendon thickness in transverse and longitudinal, using both crass position and modified crass position [37–40]. The averaged value from the 3 measurements will be recorded as the supraspinatus tendon thickness.

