### Data management {19}

Participants will receive a code number at the beginning of the study, which will be added in an excel file with all their personal information and measurements collected and analyzed (MFQ or RC), double checked (GZ, AC, or BS), and stored by the leading researcher (FHZ), protected with a password. Generated consents will be stored for 5 years after the end of the study, which will be discarded thereafter.

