## Oversight and monitoring

### Composition of the coordinating center and trial steering committee {5d}

The implementation of the trial is monitored by the researchers, composed by the main investigator (FAPHZ), which is the main liable entity for this trial and is also coordinator for the Laboratory of Clinical Research in Physical Therapy, and two other researchers responsible for the study organization, recruitment, and taking consent. In addition, there will always be two expert physical therapists in all interventions and assessment sessions. The researchers meet weekly for the appropriate course of study and to review trial conduct.

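### Data entry and analysis are declared blinded, yet the researcher who opens the allocation envelopes is one of the two named for the data file

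*Protocol article*

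**What the plan says.** Section {17a} of the protocol article describes a single-blind trial in which "The researchers responsible for outcome assessments, data entry, and statistical analysis will be blinded to the group assignments". It adds that "they will not have access to the patient’s rehabilitation place, nor to any information related to the intervention". Section {17b} gives no unblinding procedure, on the ground that only the person responsible for outcome assessment and data analysis is blinded. No blinding of participants or therapists is claimed anywhere.

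Implementation {16c} has opaque, numbered envelopes ready for use after the baseline assessments, "when the envelop will be unsealed by the researcher", who is identified by initials.

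Data management {19} describes an "excel file with all their personal information and measurements collected and analyzed". It then gives two sets of initials as alternatives, and the first is that of the envelope opener. The same sentence provides for a double check by one of three other people and for storage by the leading researcher.

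**The concern.** Participants and therapists know the treatment, so blinding of the assessment and data roles is all the masking this trial has. A person who has opened the envelopes cannot be blinded, yet the plan lets that person do work it declares blinded.

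What is at stake differs by outcome. SPADI (primary) and NPRS (secondary) are reported by participants who know their arm, so a blinded assessor protects them only to a limited degree. For these two, blinded data handling and analysis matter more, because the plan leaves choices open once data are in hand. Section {20a} makes the choice between the mixed ANOVA and the Mann-Whitney and Wilcoxon tests depend on assumption checks. Section {20c} names both a per-protocol set, defined by 80% attendance and complete assessments, and an intention-to-treat analysis with multiple imputation. Someone who knows the arms could steer these decisions, even unintentionally. Dynamometry, inclinometry and tendon thickness depend more on the operator, but they are listed only among the other outcomes.

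**Working it through.** The plan gives no figure to reproduce and no arithmetic applies. The check is whether the role assignments can all be true together. Call the envelope opener A and the other researcher named in {19} B.

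| Task | Section | Who | Status on treatment arm |
|---|---|---|---|
| Unseal envelopes | {16c} | A | Knows it, by doing the task |
| Collect and analyse measurements in the data file | {19} | A or B | A knows; B not stated |
| Double-check the file | {19} | One of three others | Not stated |
| Assess outcomes | {11a}, {17a}, {18a} | One evaluator, not identified | Declared blinded |
| Data entry and statistical analysis | {17a} | Not identified | Declared blinded |

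1. **If A handles the data.** By {16c}, A knows the allocations. By {17a}, whoever enters or analyses data does not. Both cannot hold.

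2. **If only B handles the data.** The sections are compatible, provided B is not told the allocations. Nothing in {19} restricts the work to B or says when A would do it.

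3. **Does the result turn on what {19} means by analysed?** If it means the statistical analysis, it conflicts with {17a} and {17b}. If it means only processing measurements into the file, it still conflicts with {17a}, which declares data entry blinded. The conflict remains on either reading.

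4. **Does it turn on what {19} means by collected?** If it means taking the measurements, A could be the outcome evaluator. If it means gathering completed measurements, A need not be. The text does not settle this, so nothing about the evaluator follows from it.

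5. **Do the participant codes restore blinding?** Confidentiality {27} says the code is known only to the responsible researcher. But {19} puts personal information and measurements in the same file. Anyone who opened the envelopes for the 40 planned participants and works in that file could link records to arms.

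6. **Does another section separate the roles?** None bars the envelope opener from data handling, and none mentions masked arm labels.

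**The case against.** The strongest reply is that {19} names two researchers as alternatives and adds a second-person check. If B does all the data work, the blinding holds. The phrase in {19} may also be loose wording for compiling a spreadsheet, and entering a scored questionnaire leaves little room for bias. Part of this stands: the plan permits the breach but does not require it, and the effect on data entry alone could be near zero. The double check guards against transcription errors, but it does not make the person entering the data blind.

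A reader might infer more than the text supports:

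- **That the outcome evaluator is unblinded.** Sections {11a}, {17a} and {18a} all say the evaluator is blinded, and none identifies that person.
- **That the shared site defeats the blinding.** Section {18a} says "The assessments and treatment protocols will be carried out in the Clinical Research Laboratory in Kinesiology at the university", but one laboratory can separate the two by room or time.
- **That treating therapists sit in on assessments.** Section {5d} says "there will always be two expert physical therapists in all interventions and assessment sessions". It does not say that the same two attend both kinds of session, or that they rate outcomes.
- **That ultrasound is unblinded.** The tendon section says "All ultrasound scanning will be performed by the researcher responsible of the study". No section says this person differs from the blinded evaluator or sees the allocations.
- **That A's part in recruitment matters.** Recruitment precedes allocation and does not bear on later data entry.
- **That a bias or inflated type I error can be quantified.** Any such figure would need an assumed shift and would only restate that assumption.

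**Conclusion.** The concern holds in limited form. The role list in {16c} and {19} contradicts the blinding declared in {17a} whenever the envelope opener, rather than the second named researcher, handles the data, and the protocol does not exclude this. The conflict is established for data entry or processing. It extends to the statistical analysis only if that is what {19} means by analysed.

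The text does not support saying that the trial's blinding is broken outright: a compliant division of work exists, and the evaluator at weeks 12 and 20 is never identified. The size of any bias cannot be derived from the document. The conclusion rests on two readings: that the matching initials in {16c} and {19} denote one person, and that {19} assigns tasks and does not merely list who may open the file.

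This is not a detail left to a fuller document, since the article itself assigns the roles and the assignments conflict. As written, a report could not claim blinded data entry if the envelope opener had done that work.

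**What to change.** Amend {16c} and {19} so that whoever opens the envelopes takes no part in outcome collection, data entry or analysis. Either of two arrangements would do:

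- the second researcher already listed in {19} does the data work and is not told the allocations; or
- a treating physiotherapist, who must know the arm anyway, opens the envelopes.

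If some envelopes have already been opened, only the first arrangement restores blinding for those participants. The final report should then say who entered and processed their data.

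Give the analyst a data file with masked arm labels. Align {17b} with {17a}, since the shorter list in {17b} leaves out data entry.

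The cost is a minor reassignment of tasks among existing staff and one small extra step to mask the labels. The defect shown does not require separate scheduling of assessments, exclusion of therapists from them, or re-reading of ultrasound images.

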### Procedure for unblinding if needed {17b}

There would be no reason for unblinding, since only the researcher responsible for outcome assessment and data analysis will be blinded.

## Data collection and management

### Plans for assessment and collection of outcomes {18a}

For shoulder pain all measurements will be performed on the symptomatic side. In the case of bilateral pain, the side with greater severity will be considered in the study as proposed in previous studies [16]. However, treatment will be carried out bilaterally. To minimize bias, the evaluator responsible to measure the outcomes will be blinded to the type of treatment performed. The assessments and treatment protocols will be carried out in the Clinical Research Laboratory in Kinesiology at the university. Data such as blood pressure, heart rate, saturation, and rating of perceived exertion will be measured before, after, and throughout the rehabilitation sessions. If the patient presents signs or symptoms of hypoglycemia; glycemia > 200 mg/dl or <80 mg/dl; systolic blood pressure > 180 mmHg, or diastolic blood pressure > 100 mmHg at rest, the session or evaluation will be immediately suspended, and the necessary measures will be taken. The same evaluator will perform all the tests and evaluative measures of the variables described below.

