### Outcomes {12}

The results will be evaluated at 3 points: (1) baseline (before starting the intervention program), (2) after 12 weeks of intervention (after 48 h to 1 week from the last intervention), and (3) at the week 20 (follow-up). Regarding the outcomes, the shoulder assessed by the SPADI (Shoulder Pain and Disability Index) questionnaire will be considered as primary outcome; the secondary outcome will be shoulder pain, measured with NPRS scales. Other outcomes will include range of motion, measured using a digital inclinometer; isometric shoulder muscle strength, measured using a manual muscle dynamometer; shoulder kinematics, measured using three-dimensional inertial units measurement; supraspinatus tendon thickness, measured using an ultrasound; AGE accumulation, using a skin autofluorescence measurement; and HbA1c (hemoglobin a1c), fasting glucose and lipid profile measured by a simple blood test.

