#### Shoulder pain measurement

Shoulder pain will be evaluated through the NPRS scale. The participants will be asked to report their pain level on the NPRS (0–10 scale with 0 indicating no pain and 10 indicating the worst pain). The NPRS is a widely validated single 11-point numerical scale. The data obtained through NPRS is easily documented, intuitively interpretable, and meets regulatory requirements for pain assessment and documentation [21, 22].

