#### Shoulder function measurement

Shoulder function will be evaluated using the SPADI questionnaire (Spanish validated version), which measures severity of upper extremity pain and disability during daily life activities [23]. This is a self-report questionnaire with 13 items on it (5 items specific to shoulder pain and 8 items specific to shoulder disability). The SPADI score can range from 0% indicating no pain or disability, to 100% indicating severe pain and total disability [24]. SPADI has been used previously in patients with DM [25, 26].

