### Plans to promote participant retention and complete follow-up {18b}

Researchers will be in contact with the participants during the study, through a telephone messenger group app, to solve doubts and share information. The participants will also be contacted by phone, twice/month to ask about their health status and to reinforce their participation.

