### Methods in analysis to handle protocol non-adherence and any statistical methods to handle missing data {20c}

The study will include only participants who attended at least 80% of the sessions and performed all the assessments (per-protocol). Furthermore, missing data will be handled by intention-to-treat analysis using the multiple imputation method.

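### SPADI and NPRS are self-report, but the article gives no phone fallback for a missed week-12 or week-20 visit, so values that could be observed would be imputed

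*Protocol article*

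**What the plan says.** - **Where and by whom.** Under {18a}: "The assessments and treatment protocols will be carried out in the Clinical Research Laboratory in Kinesiology at the university". The same section adds: "The same evaluator will perform all the tests and evaluative measures of the variables described below". That evaluator is blinded to treatment.
- **What is measured.** Under {12}, the SPADI "questionnaire will be considered as primary outcome; the secondary outcome will be shoulder pain, measured with NPRS scales". On SPADI, the section on shoulder function says: "This is a self-report questionnaire with 13 items on it". On NPRS, the section on shoulder pain says: "The participants will be asked to report their pain level on the NPRS".
- **Phone contact.** Under {18b}, headed as retention and complete follow-up: "The participants will also be contacted by phone, twice/month to ask about their health status and to reinforce their participation". A messenger group is also planned. No remote collection of outcomes is mentioned.
- **Expected loss.** Under {14}, 16 per group are needed and, "to account for possible withdrawals that may occur in this type of study, it will be increased by 20" per cent, giving 20 per group and 40 in total.
- **Analysis.** Under {20c}, a per-protocol set is limited to those with at least 80% attendance who did all assessments, and "missing data will be handled by intention-to-treat analysis using the multiple imputation method".
- **Attendance rule.** Under {11b}, a participant below 80% attendance is excluded from the study as a whole, not only from one analysis set.

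**The concern.** The laboratory is needed for dynamometry, inclinometry, motion sensors and ultrasound. It is not needed for a 13-item questionnaire or a 0 to 10 rating. The article ties these two outcomes to the same visit as the instrumented ones, and its retention section uses the phone channel for other purposes. Someone who cannot come to the laboratory but would answer a call therefore becomes a missing primary outcome without need.

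Week 20 looks most exposed, because it falls 8 weeks after the last session. Loss may also differ between arms: the shoulder-only sessions last 30 to 35 minutes, while the combined sessions may reach about 90. If those who stop coming differ in pain or function, and do so unequally by arm, the comparison can be biased. The 20% allowance protects power but does nothing about such bias.

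**Working it through.** **1. The plan's own figure.** Inputs from {14}: 16 per group and a 20% allowance. 16 / (1 − 0.20) = 20 per group. Alternatively, 16 × 1.20 = 19.2, rounded up to 20. Both give 40 in total, so the stated figure reproduces.

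**2. Implied effect size.** {14} gives a difference of 16.8 points, 80% power and 5% alpha, but neither an SD nor the sidedness. With a two-sided two-sample t-test (assumed) and the noncentral t distribution, 16 per group at 80% power gives d = 1.024, so SD = 16.8 / 1.024 ≈ 16.4. If the test were one-sided, d = 0.90 and SD ≈ 18.7.

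**3. Power by number observed per arm** (d = 1.024, two-sided 5%, missing participants contributing nothing):

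| Observed per arm | Lost of 20 | Power |
|---|---|---|
| 20 | 0 | 88.4% |
| 19 | 1 | 86.6% |
| 18 | 2 | 84.7% |
| 17 | 3 | 82.5% |
| 16 | 4 | 80.0% |
| 14 | 6 | 74.1% |

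The most that full recovery of the planned loss could add is 88.4 − 80.0 = 8.4 percentage points. Recovering half of it (18 per arm) adds 4.7. Because the SD is not stated, the range matters: at SD 15, power goes from 86.5% (16 per arm) to 93.2% (20 per arm); at SD 18, from 72.4% to 82.0%.

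**4. Bias, as an illustration only.** Error in an arm's mean = proportion missing × (true mean of the missing − mean of their imputed values). With 20% missing and an assumed gap of 10 to 15 points, this is 0.20 × 10 = 2 to 0.20 × 15 = 3 points, or 2/16.8 = 12% to 3/16.8 = 18% of the target difference. The gap has no source in the documents. The error in the treatment difference is one arm's error minus the other's. It is 2 to 3 points if only one arm is affected, and zero if both are affected equally.

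**5. Who is affected.** Twelve weeks at two sessions a week is 24 sessions, and 80% of 24 is 19.2. A participant who misses five sessions (19/24 = 79.2%) is therefore below the limit. Read literally, {11b} takes that person out of the study. {20c} promises an intention-to-treat analysis with imputation, in which that person should remain. A phone SPADI helps such a participant only if the two sections are reconciled. It would not restore anyone to the per-protocol set, which requires all assessments, including those that need equipment. The benefit therefore lies in the intention-to-treat analysis.

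**The case against.** The strongest reply is that this rests partly on silence. {18a} says where assessments take place; it does not forbid a phone fallback, and an article may leave the handling of a missed visit to the full protocol. That stands in part: a reader might infer that the outcomes may be collected at laboratory visits only, and the text does not say so. But the article does address the subject. {18b} is its section on complete follow-up, and it states what the phone calls are for.

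Other stronger readings also lack support:

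- **That the trial would be underpowered without the change.** The allowance already keeps 80% power with 16 observed per arm, under the plan's own assumptions. The 88% needs everyone lost in both arms to be reached, and some who withdraw will decline a call as well.
- **That imputation would rest on baseline values alone.** {20c} lists no variables for the imputation model. Week-12 SPADI could inform week 20, and pain ratings are also taken during sessions.
- **That a known bias of 2 to 3 points exists.** The gap behind it is assumed.
- **That the change costs nothing because the calls are already planned.** {18b} does not say who makes those calls or that the caller is blinded, and they concern health status and participation. {17a} keeps assessors away from information about the intervention, so using these calls could unblind the assessor.

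It is also fair to say that retention already has attention, through weekly reminders, a messenger group and the calls. These make attendance more likely, but they do not capture the outcome when a visit is missed. Finally, the attendance exclusion in {11b} may remove more outcome data than missed visits do. This is right, and it is why the fix must cover it.

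**Conclusion.** The point holds as a cheap improvement to the design and not as an error in a stated figure. With assessments placed in the laboratory and no remote route given for two self-report outcomes, a missed week-12 or week-20 visit yields an imputed SPADI and NPRS in the intention-to-treat analysis where an observed value could often be had.

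The gain is fewer imputed values in a 40-person trial and less exposure to loss that may differ by arm. Its size is unknown. The power gain is at most about 8 percentage points at the implied effect size, assuming a two-sided t-test, an SD of about 16.4 and full recovery of the planned loss. The benefit depends on {11b} not removing the same participants from follow-up.

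**What to change.** 1. **Add to {18a} and {18b}.** Anyone who misses or cannot attend the week-12 or week-20 visit, including those who have stopped sessions, completes SPADI and NPRS by phone within the visit window. For those who stopped early, count the week-12 window from the scheduled end of treatment.
2. **Keep the call blinded.** The existing blinded evaluator makes a separate call, not the routine retention call, using the same Spanish SPADI. The participant is asked at the start not to mention the sessions. This also keeps the single-evaluator rule.
3. **Record the mode of completion,** and repeat the SPADI analysis without the phone values as a sensitivity analysis.
4. **Reconcile {11b} and {20c}.** State that attendance below 80% removes a participant from the per-protocol set only, and not from outcome follow-up or the intention-to-treat analysis.

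Cost: a few sentences of protocol text, a few extra calls by the evaluator, and two modes of questionnaire completion, which the sensitivity analysis addresses. Treatment, scheduled visits and the sample size stay as they are.
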